## Abstract

**Background:**

The emergence of new problematic alcohol consumption practices among young people requires new dynamics in prevention strategies. In this context, the ADUC project (Alcohol and Drugs at the University of Caen) aims to develop a better understanding of alcohol consumption, and in particular the practice of binge drinking (BD) in students, in order to develop relevant and adapted prevention tools. The ALCOMEDIIT study (Rin Normandie and IRESP funding; Agreement 20II31-00 - ADUC part 3) is a randomized controlled trial that focuses on the specific determinant of impulsivity. The main objective of this experiment is to assess a program for the prevention of BD practices based on motivational interviewing (MI) associated with implementation intention (II) and mindfulness meditation (MBM) in a student environment.

**Methods:**

This study will include 170 healthy subjects who will be students at the university, alcohol users, with a BD score > 1 in the month preceding the inclusion but not presenting any specific disorder. The trial will be proposed by e-mail and students who meet the inclusion criteria will join either a control group which will benefit from a MI or an experimental group which will additionally benefit from an initiation to MBM with II (initial visit T0). In order to measure the effectiveness of the prevention program in terms of BD decrease, a follow-up at 1 month (T1) as well as a follow-up at 6 months (T6; exploratory) will be proposed to all participants. The total duration of this research protocol is 21 months.

**Discussion:**

The purpose of this study is to evaluate the interest of associating mindfulness meditation practices and implementation of self-regulation strategies to optimize their use, with a motivational interview in an innovative prevention program aiming at reducing alcohol use and BD practice in the student population.

**Trial registration:**

ClinicalTrials.gov Identifier: NCT05565989, September 30, 2022.

https://clinicaltrials.gov/study/NCT05565989

Protocol version 2.0 (September 2022)

No. ID-RCB : 2022-A00983-40

**Supplementary Information:**

The online version contains supplementary material available at 10.1186/s13063-023-07887-9.

## Background

Alcohol is the most consumed psychoactive substance by French adolescents [1]. Although this consumption tended to decrease over the last decade (ibid.), the emergence of new problematic alcohol consumption practices requires new dynamics in prevention strategies. In this perspective, the phenomenon of binge drinking (BD) has mobilized researchers since the 2000s. Binge drinking refers to the consumption of a large quantity of alcohol over a short period of time (6 drinks for women and 7 drinks for men in 2 hours in France). In Europe, the prevalence of BD is about 28% among students (European Union: Directorate General for Communication, 2010). The developing brain is particularly vulnerable to the effects of alcohol [2]. Indeed, if the recreational aspect of the BD may have been an illusion at first, its major consequences in personal, academic, or social terms are now relatively documented [3] as well as the brain damage and cognitive disorders associated with this practice [4–7]. Consequently, alcohol consumption among young people and binge drinking in particular are now a public health issue.

### Prevention, motivational interviewing, and impulsivity

Current prevention techniques are generally classified as environmental (e.g., maintaining a minimum legal drinking age) or individual-focused (e.g., College Alcohol Intervention Matrix, National Institute of Alcohol Abuse & Alcoholism, USA). Among the prevention techniques focused on the individual, reference is often made to methods based on motivational interviewing (MI) [8] aimed at exploring and resolving the ambivalence a person may express about his or her alcohol use in order to initiate a process of behavior change. It is interesting to note that the MI can be run as a single session lasting from 15 to 45 min [9] and that it is optimized in a face-to-face situation. This MI technique, considered by some as one of the most effective prevention techniques with a particularly optimal investment/efficacy ratio [10], is nevertheless discussed [11]. Among the explanations of the heterogeneous results usually observed, two complementary explanations can be proposed. On the one hand, studies testing the effectiveness of MI target beneficiaries with heterogeneous psychological profiles (i.e., with distinct psychological determinants specific to their consumption) in an undifferentiated way. However, various determinants have been highlighted with regard to the problem of the practice of BD [12], and not all of them are necessarily addressed or considered in a MI approach. On the other hand, the MI acts on a first necessary step for change, meaning the awareness of a risky situation, but not on the strategies allowing the implementation of the desired change. Thus, taking these two elements into consideration, we propose to combine the MI with a complementary module specifically targeting an important determinant in the context of alcohol use, namely impulsivity. The critical role of impulsivity has been identified in BD [12] and substance use in general [13]. Indeed, impulsivity, defined as a tendency for individuals to act prematurely without fully considering the consequences of their actions, is considered as a major factor associated with alcohol consumption and BD. As impulsivity cannot be considered as a unitary construct [14], its sub-dimensions have been dissociated to disentangle their respective roles [15]. Today, five facets are considered: negative vs. positive urgency (i.e., the tendency to act impetuously to regulate a negative vs. positive emotion), lack of premeditation (i.e., the tendency to favor immediate reward options without considering the potential consequences of the action), lack of perseverance (i.e., less focusing on boring or difficult tasks and distraction, and lack of interest in the future), and sensation seeking (i.e., the tendency to seek a new or exciting experience).

To target the drinking processes specifically related to impulsivity, Larsen and Hollands’ (2021) theoretical model [16] proposes different prevention techniques to regulate the automatic processes underlying maladaptive behavior that can be harmful to health. The ALCOMEDIIT module is based on two antecedent-focused strategies that aim to avoid exposure to or activation of automatic (i.e., impulsive) responses that lead to alcohol consumption.

### Mindfulness intervention

First, the ALCOMEDIIT module will offer an initiation to mindfulness meditation (MM), a so-called indirect strategy aimed at modifying unwanted automatic responses by strengthening self-control skills, especially by automating self-control processes as well as by facilitating a more efficient executive functioning ensuring cognitive and behavioral control mechanisms. Indeed, a possible tool to fight against impulsivity towards the desire to consume alcohol is MM [17]. MM is described as “the awareness that emerges from purposefully paying attention, in the present moment and without judgment, to the unfolding of experience from moment to moment” [18]. MM-based interventions have already proven to be effective in reducing a variety of substance uses, particularly in an adult population [19]. More specifically, the Mindfulness Based Relapse Prevention (MBRP) program has demonstrated its clinical value in terms of reducing the desire to use drugs and the risk of relapse in people who received inpatient or outpatient treatment in an addiction clinical center [20]. However, this type of program requiring an 8-week investment would be difficult to integrate into a prevention approach aimed at regulating alcohol consumption and binge drinking in the student population because of its cost in terms of time and the mobilization of healthcare personnel. To date, very few studies have examined the usefulness of a brief intervention based on MM principles as part of a prevention program for students who are not in the process of treatment. To our knowledge, only one exploratory study has attempted to evaluate the effectiveness of a mindfulness-based brief intervention for students with binge drinking [21]. This first study yielded promising results highlighting the effectiveness of MM in decreasing the frequency of BD use and reported negative consequences related to alcohol consumption as well as in increasing feelings of self-efficacy and mindfulness (i.e., the willingness to pay attention to and accept the experience of the present moment as it is). Nevertheless, these results need to be replicated given the relatively small sample size. In addition, this study has some limitations and questions that the ALCOMEDIIT prevention program will attempt to address. Indeed, the ALCOMEDIIT project is not limited to a 1-month follow-up but also includes an exploratory 6-month follow-up offering the possibility to test the potential beneficial effects of the prevention program over time. Apart from the 1- and 6-month follow-up sessions, information concerning alcohol consumption and daily practice of MM can be collected in an ecological way within a mobile application allowing to prevent possible mnemonic biases often generated by retrospective recall of memories at a distance from the event. The ALCOMEDIIT project also places the control group in a brief intervention condition by having all the participants benefit from a motivational interview, thus making it possible to determine the specific benefits linked to the MM intervention.

### Implementation Intentions and volitional help sheets

Second, the potential benefits expected from this practice of MM on the clinical issue of alcohol consumption in the student population could be optimized by the use of implementation intentions (II). This strategy aimed at limiting unwanted automatic responses through the planification of the suppression, avoidance, or replacement of specific stimulus-response associations. For example, in the ALCOMEDIIT project, the aim is to choose different everyday situations frequently associated with alcohol urge or consumption and to plan to practice mindfulness meditation. By automating the practice of a breathing exercise in a tempting situation, it may reduce the desire to drink and the feeling of craving or reduce the consumption of the substance. Indeed, once people are able to use a MM exercise to contain their urge to consume alcohol, they can plan through implementation intentions to develop their MBM skills [22–24] on the one hand, but on the other hand, they can be trained to identify risky situations, even cravings, in order to plan [25] to regulate their consumption by using MM [26]. The implementation intention technique (II) allow to “go beyond” a mere motivation to act that define what the individual wants to do (e.g., “I want to control my alcohol consumption”), by contextualizing this objective and specifying the action modalities to achieve it. In other words, with this technique, the individual link situational cues (e.g., a place, a moment and/or a mental state) to a goal-directed-response (an emotional, cognitive or behavioral response) to be implemented in response to this stimulus (in our case, a GPA exercise to curb the impulsive drinking reaction). This “situational cues/goal-directed response” link is actualized in the verbal format “if the situation X arises, then I will perform the goal-directed response Z” [27, 28]. This association makes the situational cues more cognitively accessible [29] and automates the response enactment [30]. Thus, the implementation of the objective no longer requires additional elaboration or decision making that could be interfered with by other cues.

In short, the ALCOMEDIIT trial will consist of training people to combine two complementary psychological techniques. First, the capacity for mindfulness will be exercised. Then, persons will form implementation intentions to control their consumption (e.g., [31] for an example targeting BD intentions) by identifying alcohol related situational cues and planning to perform actions related to mindfulness skills. In other words, the objective of ALCOMEDIIT is to give people tools to fight their impulsive tendency to drink (through the development of their mindfulness skills) and to provide them with the psychological equipment to automate the use of these tools (through the adoption of intention implementation techniques).

## Methods/design

### Study objectives

The primary purpose of this work is to evaluate the interest of associating mindfulness meditation practices and implementation of self-regulation strategies to optimize their use, with a motivational interview in a prevention program aiming to prevent binge drinking in the student population. The program will be evaluated by regular self-reported follow-up by the subjects on a non-connected mobile application based on an ecological momentary assessment (EMA [32]) in the medium term (+ 1 month) and in an exploratory way in the long term (+ 6 months).

The secondary objectives are, beyond preventing the practice of BD, to explore the potential further beneficial effects of this prevention program in the medium term (1 month) and long term (6 months; exploratory) on alcohol-related elements (weekly alcohol use, BD, motivation to regulate alcohol use, craving).

### Study design and setting

All the study design and setting (see SPIRIT Checks in Additionnal File 1) has been elaborated by the trial steering committee (TSC) which is made up of the research team who authored this article, with the exception of Messrs [name] and [name], who were respectively responsible for the development and design of the ALCOODUC mobile app. The TSC, comprising nine people, is made up of academics specializing in prevention issues and field experts specializing in alcohol-related problems and/or the practice of mindfulness meditation. This steering committee met on a monthly basis during the protocol design phase and validated each stage of the protocol submission process, notably at the level of the national ethics committee (see the “Ethics approval and consent to participate” section for a brief description of the French system).

This is a randomized controlled study in parallel groups. It will compare the monthly BD score between the control group and the experimental group, and the allocation ratio is 1:1.

One hundred seventy volunteer participants from the University of Caen (France) will be included in this research protocol (see Fig. 1). During the initial visit, after presentation of the study and signature of the consent form presented by one of the two psychologists in charge of the interviews, all participants will complete various online questionnaires (estimated completion time 40 min; LimeSurvey) as well as a screening for neuropsychological impairments using the BEARNI tool (Brief Evaluation of Alcohol-Related Neuropsychological Impairments [33]; estimated completion time of 20 min). Eighty-five participants will benefit from the control condition (i.e., a motivational interview), and 85 other participants will benefit from the experimental condition (i.e., a motivational interview associated with a mindfulness meditation session and intention implementation; estimated duration 1 h).

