**Fig. 1 Fig1:**
[figure not shown]
Flux diagram and procedure

During follow-ups at 1 month and then at 6 months, alcohol-related questionnaires from the initial visit will be offered again online (LimeSurvey) to the 170 participants to allow for the longitudinal evaluation of these different measures. In addition, all students will be asked to answer regular questionnaires based on Ecological Momentary Assessment (EMA) on an offline mobile application in order to evaluate the monthly BD score (main criterion) and the weekly amount of alcohol consumed and to follow their mindfulness meditation practice (only for the experimental group). This data collection will be done between the different sessions (initial visit “T0” and follow-ups at 1 month “T1” and at 6 months “T6,” the latter being exploratory). All data, including LimeSurvey questionnaires, are hosted on servers at the University of Caen, France.

Randomization will be organized by placing 170 sealed opaques envelopes in which the participant’s group (control vs. experimental) will be specified. After completion of all measures in T0, participants select an envelope from a series of envelopes in a box at their disposal. The ignorance clause will hence be respected. The psychologists in charge of the interviews will be blind until the opening of the envelope drawn by the participant at the end of T0.

The inclusion phase incorporated the possibility of a substantial attrition rate (about 30%) to ensure sufficient statistical power. Therefore, trial exits (refusal to continue^1^, withdrawal of consent, or other) will not be replaced.

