### Recruitment of participants and material

Participation in the study will be proposed to all students of the University of Caen through their institutional email address. In this email, the study will be briefly presented and a link to a LimeSurvey questionnaire will be proposed. On this link, the research and its objectives will be presented in more details, followed by questions on the elements of inclusion and exclusion.

Based on their responses, volunteers may or may not be included in the study sample. An email will inform them of this decision and the volunteers who meet the inclusion criteria will be invited to contact one of the investigating psychologists to schedule the inclusion visit.

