#### Control group

Participants in the control group will receive no specific psycho-social intervention except that they will benefit from a motivational interview with the psychologist who welcomed them for inclusion.

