#### Experimental group

Similar to the control group, participants will benefit from a motivational interview with the psychologist who welcomed them for inclusion. Yet, this motivational interview will be completed by two activities: mindfulness-based initiation and implementation intention exercises.

The mindfulness meditation session is structured in four steps. The session begins with the meditation called “grape exercise” associated with the “sound meditation.” In a second step, the principles of mindfulness meditation (conceptualization of MBM, autopilot and acceptance) are explained to the participants by the psychologist. The session continues with two exercises, the first named “Sitting Meditation Space on thoughts” and the second “SOBER Breathing Space in the face of 1 Challenge situation.” At the end of the session, an explanation on the memo sheet available on the mobile application is given to the participants so that they can continue their practice if a risky substance use situation arises.

The implementation intention session follows the MBM initiation. It focuses on the implementation of two behaviors, on the one hand, regular MBM-based training (II-1) and, on the other hand, the use of MBM in risky drinking situations (II-2). The two systematic phases related to an II process are specific to each of the two implementations (all details available on osf: https://osf.io/3n4c6/.

II-1 deals with the implementation of a daily and/or regular use of MBM. It focuses first on the identification by the participant of a situation, in terms of place, moment of day, and context, which represents an opportunity to reach the goal of practicing MBM on a regular basis, or an obstacle to reaching this goal (II-1a). Then, the participant is invited to identify a thought or behavior that is relevant, for him or her and in this situation that he or she has chosen, to seize this opportunity or overcome this obstacle (II-1b). On this basis, the participant is invited to explicitly formulate the link between these two elements in the linguistic format “If (II-1a), then (II-1b),” to copy it once, to repeat it quietly in his/her head 3 times while trying to represent the scene concretely. The participant must repeat the exercise a second time by proposing another “II-1a” and another “II-1b.”

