A second step will consist in conducting the main analyses. Recall that by “five dependent variables (DVs),” we mean here binge drinking score (BD), weekly alcohol consumption (WAC), craving, impulsivity, and readiness to change (RC). Prior to the main analyses, we will check whether there is a significant relationship between age and the baseline scores of any of the five DVs. We expect the age range to be rather small apart from potential serious outliers, in a sample that is not particularly large, and we do not expect age to play a noticeable role on most of the DVs, except for BD scores where it is suspected that binge drinking behaviors are most common in the younger population. For these reasons, we want to avoid adding age as a covariate unless the data show that we really have to. We will conduct five similar general linear analyses, with the following variables: dependent variable: evolution scores (T0 → T1) of one of the five DVs; factors: condition, sex, condition*sex; covariates: AUDIT score, baseline of the DV at hand. Covariate(s) that will be added if either they are significantly related to the baseline scores of the DV at hand, or the two groups were not matched at T0 with respect to them: age, trait anxiety level, depression level. We add as a covariate the baseline of the DV at hand because we expect that the higher level of self-consciousness brought by the very fact of taking part in this demanding study might trigger an effect of regression to the mean, by which people with a larger baseline score (and hence a larger margin for improvement) would show better results no matter in what condition they were placed.

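### Two psychologists conduct the interviews in both arms, but the stated models have no psychologist term: a small, cheaply recovered loss of precision, not a bias

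*Protocol article*

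**What the plan says.** Under Study design and setting, the protocol article says the consent form is presented by "one of the two psychologists in charge of the interviews". Under Recruitment of participants and material, eligible volunteers "will be invited to contact one of the investigating psychologists to schedule the inclusion visit". The Control group section says that "they will benefit from a motivational interview with the psychologist who welcomed them for inclusion", and the Experimental group section ties the interview to the same person: "participants will benefit from a motivational interview with the psychologist who welcomed them for inclusion". In the experimental arm a psychologist also explains the principles of mindfulness.

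Allocation comes after the T0 measures, when "participants select an envelope from a series of envelopes in a box at their disposal". No stratification by psychologist is described.

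The Data management and analysis plan section gives the model for each of the five dependent variables: "factors: condition, sex, condition*sex; covariates: AUDIT score, baseline of the DV at hand". Age, trait anxiety and depression may be added under stated conditions. Psychologist is not in this list, nor among the variables checked for balance at T0, nor among the parameters described for the power simulation.

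**The concern.** Motivational interviewing depends on who conducts it, and here that person is one of two and identifiable for every participant. If one psychologist obtains larger reductions in binge drinking than the other, the stated model treats that difference as unexplained noise. If the arms by chance draw unequally on the two psychologists, part of the difference also enters the estimated condition effect.

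The article writes out the factors and covariates itself, including some that are added only conditionally. The absence of a psychologist term is therefore a feature of the stated model, not a detail left to the analysis plan. What is at stake is some precision, and a clearer view of how far a result obtained with two people carries over to other prevention services, which the Dissemination policy section has in mind.

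**Working it through.** **Order of events.** The volunteer contacts a psychologist, attends the inclusion visit, completes the T0 measures, draws an envelope, and then has the interview. The psychologist is fixed before allocation, so which psychologist a participant sees cannot depend on the arm.

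**Inputs from the article.** Two psychologists; 1:1 allocation; 170 included; 120 needed for analysis; power stated as above 0.80 at alpha 0.05.

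**Assumptions (the article gives no figures).** Completers split 60 to 60 by arm and 60 to 60 by psychologist; the psychologists' results differ by 0.3 to 0.5 SD; intraclass correlation (ICC) 0.01 to 0.10.

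**Chance imbalance.** The number of one psychologist's participants in the experimental arm is hypergeometric (120 in total, 60 with that psychologist, 60 in the arm).
- Mean = 60 × 60/120 = 30.
- Variance = 60 × 0.5 × 0.5 × 60/119 = 7.56, so SD = 2.75.
- 95% range: 25 to 35 of 60, or 41.7% to 58.3% of an arm.
- Between-arm difference in share at that edge: 58.3 − 41.7 = 16.7 points (10/60). At one SD: 2 × 2.75/60 = 9.2 points.

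An even caseload is the less favourable assumption. With all 170 envelopes drawn, the SD of the difference in share is 7.7 points for an 85/85 caseload and 7.0 points if one psychologist sees only 50.

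**Shift in the condition effect** (difference in share × difference between psychologists).
- Edge of the 95% range: 0.167 × 0.3 = 0.05 SD; 0.167 × 0.5 = 0.08 SD.
- One SD: 0.092 × 0.3 = 0.03 SD; 0.092 × 0.5 = 0.05 SD.
- Standard error of the condition effect with 60 per arm: √(2/60) = 0.18 SD. The edge shift is thus 0.27 to 0.46 of one standard error.

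**Precision gained by adjusting.** Fitting psychologist multiplies the residual SD by √(1 − ICC). Power of exactly 0.80 with 60 per arm corresponds to d = (1.96 + 0.84) × √(2/60) = 0.51.

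| Assumed ICC | Power without term | Power with term |
|---|---|---|
| 0.01 | 0.800 | 0.804 |
| 0.02 | 0.800 | 0.808 |
| 0.05 | 0.800 | 0.820 |
| 0.10 | 0.800 | 0.840 |

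The 0.80 is only a reference point. The Gamma parameters are not given, and I could not reproduce the figure from the parameters that are: 0.1B/(0.25B + 0.5) is always below 0.4, and two-sided power at d = 0.4 with 60 per arm is 0.591. That is a separate matter and does not change this one. Starting from 0.591, the term brings power to between 0.596 and 0.637 over the same ICC range.

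**What a look by psychologist can show.** With about 30 per cell, the condition effect within one psychologist has a standard error of √(2/30) = 0.26 SD. The difference between the two psychologists' effects has √(4/30) = 0.37 SD.

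**The case against.** The strongest defence is that nothing here is invalid. Both psychologists appear to serve both arms, allocation follows the choice of psychologist, and leaving out a prognostic main effect in a randomised comparison costs precision without invalidating the test. Chance imbalance is already reflected in the standard error, and the 0.05 to 0.08 SD figure is the edge of a 95% range multiplied by an assumed difference. All of this stands, and it limits the point to a precision improvement.

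A reader might infer more, and the article does not support it:
- That participants choosing their psychologist biases the comparison. It cannot, because the choice precedes the draw. Nor does the article say who decides which psychologist is contacted.
- That the two psychologists deliver the whole programme. Only the motivational interview is tied to the including psychologist. Nobody is named as leading the implementation-intention session, and the app supplies exercises afterwards.
- That an effect confined to one psychologist would go unexamined. The article announces an exploratory stage and a separate analysis plan, neither of which is shown.

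It is also fair to object that a main-effect term does not answer whether the programme works equally well with each psychologist, and that a comparison with about 30 per cell could rarely tell. That is why the breakdown below is descriptive only.

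**Conclusion.** The point holds as a minor, inexpensive improvement to a stated model. The condition effect is not biased. The omission leaves between-psychologist variation in the residual and in chance imbalance: a shift of up to about 0.05 to 0.08 SD at the edge of the 95% range, and a power gain forgone of about 0.4 to 4 points from the stated 0.80. These sizes rest on assumed values for the psychologist difference, the ICC and an even split of 120 completers. The sample size need not change. Two psychologists also limit generalisation to others who might deliver the programme, and no model term removes that limit.

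**What to change.** Record the psychologist for each participant. Before analysis, add psychologist as a two-level fixed factor to the models in the Data management and analysis plan section, for both the T1 and the T6 evolution scores. Two levels are too few for a random effect. Report the condition effect with its confidence interval separately for each psychologist, labelled as descriptive, and state that about 30 participants per cell gives low precision. State as a limitation that two psychologists restrict how far the result generalises.

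The cost is one degree of freedom per model and one table. The adjustment can cover everyone, including those already enrolled (98 of 170 in the Trial status section). I would leave the envelope procedure as it is: a separate series for each psychologist, introduced mid-trial, could make late draws more predictable to the person running them.
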